Evaluation of the exposure to exposure (E2E) training intervention took place in two phases. The first phase was a case-series analysis (*N* = 6 therapists) intended to fine-tune training procedures and establish the necessary dose of experiential training for therapists’ negative belief levels to reach an *a-priori* benchmark. The second phase was a randomized trial (*N* = 36 therapists) testing whether the targeted E2E training approach, relative to didactics alone, was a more potent intervention for reducing negative beliefs. Specifically, it was hypothesized that therapists in the E2E training condition would evidence significantly lower negative beliefs about exposure relative to the didactic condition at post-workshop. As an added layer of rigor, levels of general beliefs about EBP were measured along with negative beliefs at pre-, mid-, and post-workshop to demonstrate the specificity of the E2E condition’s effect on the planned target (i.e., negative beliefs) while exhibiting comparable levels of EBP belief change relative to the didactic condition. It was also hypothesized that negative belief change during the workshop training would be associated with therapist delivery behavior when implementing exposure with anxious patients in the consultation phase of the study, such that greater reduction in negative beliefs would be associated with: (1) a higher rate of optimal delivery behaviors, (2) a lower rate of suboptimal delivery behaviors as measured by both self-report and observational coding data, and (3) a higher rate of exposure utilization across sessions. A detailed accounting of study methods, practical adjustments, and other implementation considerations are presented below.

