**Figure 3 fig3:**
[figure not shown]
Training activities, hypotheses, and measurement strategy. EBPAS = Evidence Based Practice Attitudes Scale; TBES = Therapist negative Beliefs about Exposure.

**Table 1 tab1:** Measurement strategy and timepoints.

Measure (*Objective*)	Timepoint					
	Baseline	End of core didactics	During experiential (E2E only)	End of workshop	Consult	End of study
TBES (*Primary target*)	X	X		X		X
EBPAS (*Target specificity*)	X	X		X		X
Knowledge (*Candidate target*)	X	X		X		X
Self-efficacy (*Candidate target*)	X	X		X		X
BES-T (*Target process*)			X			
Training satisfaction (*QI*)				X		X
EPCS (*Outcome*)					X	

BES-T = Beliefs about Exposure Scale – Training; EBPAS = Evidence Based Practice Attitudes Scale; EPCS = Exposure Process Coding System; Knowledge = Exposure Knowledge Measure; Self-Efficacy = Measure of Exposure Delivery Self-efficacy; TBES = Therapist negative Beliefs about Exposure; Training Satisfaction = Training Acceptability Rating Scale (TARS).

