## Anticipated results

The primary goals of this study are to first establish and then confirm engagement of the negative beliefs target with the novel E2E training approach, and to also demonstrate a relationship between change in the beliefs target and therapists’ in-session delivery behaviors. Target engagement was established during the Phase 1 trial. The Phase 2 training trial will confirm target engagement by demonstrating significantly greater change in belief scores following workshop training for therapists assigned to E2E relative to the didactic group (Hypothesis 1). To test this effect, group status (E2E vs. didactic) will be entered as a predictor of post-workshop total TBES score while including a random intercept for TBES baseline score. It is anticipated that as TBES-measured belief levels approach zero, the distribution will become positively skewed. This is problematic given the goal to target and reduce belief levels as close to zero as possible. To account for the positive skew of TBES scores approaching zero, binomial-based modeling will be used to conduct a logistic regression to assess for a difference in belief reduction between those in the didactic and E2E groups following the workshop training. Figure 3 illustrates the measurement time points and pathways for testing planned hypotheses.

It is also expected that the E2E intervention will produce a specific change in negative beliefs (measured pre-and post-workshop) about exposure but not differentially affect broader beliefs about EBPs (EBPAS) in general (Hypothesis 2). Target specificity will be demonstrated by significantly greater levels of negative belief change but comparable levels of EBP belief change in the E2E group relative to didactic. The pilot nature of this study does not allow sufficient statistical power to conduct a non-inferiority test of group differences on EBPAS change, so comparison of descriptive statistics will provide initial evidence of specificity to be fully tested in a larger trial (61, 62).

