The relationship between target change (i.e., reduction in negative beliefs) and outcomes of interest will be evaluated using the EPCS micro-analytic coding system for categorizing in-session exposure delivery behavior (Hypothesis 3). Therapist delivery behaviors during the consultation phase of training will be categorized into “optimal” (i.e., delivery behaviors intended to engage and intensify patient anxiety) and “suboptimal” (i.e., delivery behaviors intended to artificially reduce patient anxiety) categories in accordance with previously established procedures (54). Rates of optimal and suboptimal delivery behaviors will be calculated for each therapist with recorded session data, and in-session behavior will be examined as a function of post-training TBES scores using GLM (Gaussian distribution); these will be conducted as two separate tests examining optimal and suboptimal behaviors. Finally, the relationship between negative beliefs and rates of exposure utilization, calculated as a percentage of sessions with and without exposure delivery, will be assessed using correlational analyses consistent with past training trials incorporating the EPCS coding system [(54, 55); Hypothesis 4].

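### Hypothesis 3 is about reduction in negative beliefs, but its stated model uses the post-training TBES score with no baseline term, so it cannot separate change during training from differences that predate it

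*Protocol article*

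**What the plan says.** The hypothesis is worded as change throughout the protocol article.

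- The Abstract (Anticipated results) links a larger fall in negative beliefs to better coded delivery.
- Current study: "negative belief change during the workshop training would be associated with therapist delivery behavior", in the direction that "greater reduction in negative beliefs would be associated with: (1) a higher rate of optimal delivery behaviors", with fewer suboptimal behaviours and more use of exposure as the second and third parts.
- Anticipated results, first paragraph, gives as a main goal of the study "to also demonstrate a relationship between change in the beliefs target and" in-session delivery.
- Anticipated results, Hypothesis 3 paragraph, opens: "The relationship between target change (i.e., reduction in negative beliefs) and outcomes of interest will be evaluated".

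The same Hypothesis 3 paragraph then sets the analysis: "in-session behavior will be examined as a function of post-training TBES scores using GLM (Gaussian distribution". There are two such tests, one for optimal and one for suboptimal behaviours. Neither a baseline TBES term nor a change score is mentioned. Baseline TBES is mentioned only in the Hypothesis 1 model.

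Table 1 ("Measurement strategy and timepoints") shows TBES at baseline, end of core didactics, end of workshop and end of study.

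On the outcome side, Current study says delivery will be judged "as measured by both self-report and observational coding data". Table 1 lists only the EPCS at the consultation stage, and the Hypothesis 3 analysis names only the EPCS. The therapist-completed Exposure Guide is described under Treatment delivery and consultation measures but appears in neither place.

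**The concern.** The quantity in the hypothesis and the quantity in the model differ. A post-training score is the sum of where the therapist started and how far the therapist moved. With no baseline term, a therapist who always thought well of exposure and did not change is treated the same as one whom training brought to that point.

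This bears on the study's central argument. The article presents the trial as a mechanism test in which moving the target should move the outcome. An association with post-training level could arise wholly from stable differences between therapists. Such differences are plausible here, since the Current study section says that negative beliefs vary with prior specialised training, education and caseload. A real change effect could also be missed if post level tracks change poorly.

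**Working it through.** The article gives no sample size, power, SD or pre-post correlation for Hypothesis 3, so there is no figure of its own to reproduce. The finding rests on the text. The figures below only show how much could turn on it, and all their inputs are assumed.

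**1. How closely post level tracks reduction.** Let r be the pre-post correlation and k the post SD divided by the pre SD. Reduction is pre minus post. Then

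corr(post, reduction) = (r − k) / √(1 + k² − 2rk), and shared variance is its square.

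Example, r = 0.5 and k = 1: (0.5 − 1)/√(1 + 1 − 1) = −0.50, so 25%. Example, r = 0.3 and k = 1.5: (−1.2)²/(1 + 2.25 − 0.9) = 1.44/2.35 = 61%.

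| k | r = 0.3 | r = 0.5 | r = 0.7 |
|---|---|---|---|
| 0.7 | 15% | 5% | 0% |
| 1.0 | 35% | 25% | 15% |
| 1.3 | 52% | 46% | 41% |
| 1.5 | 61% | 57% | 56% |

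The article does not settle k. Scores piling up near zero could shrink the post SD. A sample chosen for high baseline beliefs, with arms that separate after training, could widen it relative to baseline.

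**2. What this does to the test.** Simulation with 5,000 runs per cell and two-sided 0.05. Assumed: n = 21 therapists, k = 1, a slope of 1 baseline SD, residual SD 1. The number of therapists with recorded sessions is not given; 21 is the number of patients recruited at the time of writing and serves only as a middle value. Rejection rates for r = 0.3 / 0.5 / 0.7:

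| Truth | Post only | Raw change score | Post given baseline |
|---|---|---|---|
| Delivery depends on baseline beliefs only | 15 / 36 / 66% | 49 / 37 / 22% | 5 / 5 / 5% |
| Delivery depends on change only | 56 / 36 / 19% | 99 / 97 / 87% | 95 / 91 / 81% |

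Across n = 15 to 36 the post-only test rejects 11% to 89% of the time in the first row, and the adjusted test 4.5% to 5.5%. The post-only and adjusted figures in the first row do not depend on k: rescaling the post score leaves both tests unchanged, and corr(post, delivery) is −r/√2, that is −0.21, −0.35 and −0.49. A raw change score alone does not cure the problem, because it is correlated with baseline.

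**3. Why adding baseline answers the question.** In the model delivery = a + b·post + c·pre, substitute post = pre − reduction:

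delivery = a − b·reduction + (b + c)·pre.

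So −b is the association of delivery with reduction among therapists with the same baseline. For optimal behaviours the hypothesis predicts b below zero, for suboptimal behaviours b above zero.

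**The case against.** Four points can fairly be made on the other side.

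- **Other covariates are not excluded.** The article names a predictor without saying that it is the only term, and covariate lists are often left to an analysis plan. Figure 3, which is said to show the paths for testing the hypotheses, is not visible. This limits the wording: no baseline term is stated. It does not remove the conflict, because the paragraph itself names reduction as the exposure and then gives a level as the predictor.
- **Residual level is a coherent mechanism variable.** The Introduction attributes continuing suboptimal delivery to beliefs that remain after didactic training, and Phase 1 judged therapists against a post-workshop TBES criterion. If that is what is meant, the hypothesis should say so. As it stands, the Abstract, Current study and Anticipated results all say reduction.
- **Pilot status.** The Discussion disclaims a powered comparison of groups, but it relies on these planned analyses to judge whether the target-outcome relationship holds. The disclaimer does not cover a mismatch between hypothesis and predictor.
- **The figures depend on assumptions.** This stands. A reader who looked only at SD ratios of 1 and below might infer that the post score barely measures change, or that the link between change and delivery goes untested. The documents do not support that: ratios above 1 are equally open, and they give 41% to 61% shared variance.

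**Conclusion.** The point holds in this form: Hypothesis 3 concerns reduction in negative beliefs, the only model stated uses the post-training TBES score without a stated baseline term, and that model cannot separate change during training from differences that predate it. The textual conflict needs no assumption. Its size does: shared variance between post score and reduction runs from about 0% to 61% for r of 0.3 to 0.7 and k of 0.7 to 1.5, and the simulated error rates also rest on an assumed slope and sample size.

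Two further inferences go too far. One is that Hypothesis 4 has the same error: its analysis refers only to negative beliefs and fixes no TBES time point or form, so it is loosely worded rather than shown to be wrong. The other is that a baseline-adjusted coefficient would give the effect of change: therapists are randomised to training, not to beliefs, so it remains an association.

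The missing self-report analysis is a smaller, separate inconsistency.

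**What to change.** 1. State the Hypothesis 3 model as delivery rate on end-of-workshop TBES plus baseline TBES, separately for optimal and suboptimal rates. Replace the term post-training with end of workshop, since Table 1 also has an end-of-study TBES. Read the post coefficient as the association of delivery with belief change given baseline, not as causal.
2. Report a version that also adjusts for condition only as a sensitivity analysis, because it removes the between-arm belief difference that randomisation creates.
3. Word Hypothesis 4 to match, for example as a partial correlation of utilization with end-of-workshop TBES given baseline TBES, because Current study states that part as reduction too.
4. Either list the Exposure Guide at Consult in Table 1 and analyse its own quality ratings with the same model, or delete self-report from the hypothesis. The optimal/suboptimal split is described only for EPCS-coded behaviours, so it should not be assumed for the Guide.

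Cost: a few sentences, possibly one table row, and one degree of freedom (n − 2 to n − 3 residual; 19 to 18 at the assumed n = 21), with one more in the sensitivity model. That is not negligible in a small sample. Baseline TBES is already in the measurement schedule and was taken before training. The delivery data are still being gathered, since Phase 2 is described as ongoing and the coding as still to come, so the change can be made before those results are known.

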## Discussion

Despite evidence to support exposure therapy as a frontline treatment for anxiety disorders and OCD it is highly underutilized and often suboptimally delivered in typical practice, even among therapists who have received specialized training in the delivery of exposure therapy (9, 26). A noted barrier to dissemination is therapists’ negative beliefs about the dangerousness and intolerability of exposure therapy for their patients. Preliminary studies have investigated approaches to augmenting negative beliefs during treatment (36, 38, 39), and revealed active strategies such as experiential activities appear to change beliefs above and beyond standard didactic training. The current study aims to apply the same well-validated behavioral strategies used to reduce patient negative beliefs during exposure to target therapists’ negative beliefs and delivery behavior; thus, training was conceptualized as “exposure to exposure.” The study design follows the principles of experimental therapeutics and guidelines put forth by the precision implementation framework for mechanisms of implementation interventions. Findings from the present study will provide a template for applying a rigorous mechanism testing framework on training intervention research, and may help guide the development of targeted training interventions for other EBPs. Due to the pilot nature of this training intervention development project, the sample is not intended to represent a fully powered test of group differences. Instead, the rigorous measurement strategy and planned analyses based on empirical benchmarks provides a strong procedure for determining whether the assumptions of an experimental therapeutics approach are initially met (i.e., target engagement, target-outcome relationship), and can be confirmed in a larger, fully powered training trial.

### Implementation challenges and recommendations

There is strong evidence to support organization-level factors such as implementation climate and transformational leadership as key factors in the successful implementation of evidence-based practices in community settings [e.g., (63, 64)]. However, these organizational factors are not universally supportive of all evidence-based practices and additional research is needed to better understand the unique organization factors that support implementation of exposure therapy (35).

Two significant organization-level factors that influenced the course of this study were changes in partnering clinic sites and significant turnover among both organization leadership and participating therapists.

#### Site changes

Agency 1 provided in-home services at four clinic sites split across two different service divisions. Originally, the study was partnered with two clinic sites led by a division leader that strongly supported training in EBPs and the goals of the current project. Unfortunately, after Phase 1 activities were complete the study team was informed that both partnering clinic sites were closing imminently. The division leader connected the study team to the division leader in charge of the two remaining home-based clinic sites, and the study team quickly pivoted to plan the Phase 2 training trial with a new set of division and program leadership. While many aspects of the programs remained consistent, there were aspects of the supervisor role that differed and influenced study recruitment procedures. Specifically, supervisors at the two new sites were much more involved in case assignments than at our original two sites, and because this was not detected in our rapid onboarding process with the two new sites, supervisors did not receive enough information about identifying and referring relevant study cases to assist with recruitment. This experience underscores the importance of supervisor involvement in successful training implementation efforts (65, 66).

#### Turnover

Initiation of the phase two randomized training trial coincided with the onset of COVID and required a retooling of all planned in-person components to occur remotely (i.e., consenting, measure administration, recruitment, and all training and consultation activities). After piloting and obtaining IRB approval for remote study procedures, the first training was well-attended because therapists were struggling to generate clinical revenue while clinics transitioned to remote care options. Thus, therapists eagerly signed up for the training but had few patients to refer for the consultation component, which contributed to patient recruitment difficulties early in phase two. Relatedly, the “great resignation” (67) occurred during the trial and 57% of trained therapists left their organization during phase two, which again affected patient recruitment rates. Patients were recruited to the study to allow for in-session measures of therapist delivery behavior following training, so patient participants needed to be assigned to a study therapist in order to be eligible for participation. As therapist turnover escalated, the pool of eligible participants shrunk and necessitated an over-recruitment of therapists (36 trained therapists rather than 26 originally proposed) in order for patient recruitment to continue.

Although resources exist to help guide a thorough needs assessment prior to initiating implementation activities in a partnering organization [e.g., (68)], there is much less guidance for implementing therapist training interventions in collaboration with CMHAs. Based on implementation experiences in the current study, it is recommended that early assessment and planning include a thorough understanding of how agency personnel are related hierarchically and with regard to clinical tasks relevant to the study intervention. If there are changes to partnering agencies, sites, or key personnel, as is common when conducting community-based training interventions, it is worth reassessing the organization hierarchy and job duties of all relevant staff to prevent some of the implementation challenges encountered in this study.

### Parallel treatment and E2E training processes

The E2E concept under investigation in the current study provides a template for leveraging existing behavior change strategies validated in clinical practice to move patterns of practice behavior following EBP training interventions. While the present study provides an innovative framework for intervening on therapists’ anxious negative beliefs using experiential training tasks, there are several ways in which exposure principles could be further infused in expanded future tests of the E2E training approach.

#### Assessment

Consistent with assessment of patient symptoms at the outset of treatment, trainers should measure therapist negative beliefs before initiating workshop training to understand the type and extent of therapists’ anxious negative beliefs and tailor didactic and experiential materials accordingly. In the present study beliefs were sampled prior to initiating training to establish a baseline for evaluating change during didactic and experiential portions of the training, but that information was not used to tailor aspects of the workshop. Future iterations of E2E could use baseline beliefs measures to prioritize specific talking points during didactic instruction and focus more time on specific types of experiential tasks. For instance, a therapist endorsing few reservations about the safety of exposure but some concern about patients getting upset during exposure tasks might benefit most from didactic information that presents patient testimonials and experiential tasks in which their partner purposely expresses reservations about an exposure task so the therapist can practice rolling with resistance and titrating the task to be appropriately palatable for the practice partner.

#### Education

Another important parallel process to leverage in future E2E interventions is the link between training didactics and treatment psychoeducation. In both exposure treatment and training, the goal is to ensure individuals understand how and why exposure works to correct anxious beliefs and to set accurate expectations for how to optimize exposure effectiveness. At the outset of treatment, therapists often solicit patient feedback to ensure they understand the concepts and agree with the rationale before proceeding with exposure tasks; future training efforts should include similar learning checks throughout initial didactic components to promote full engagement with ensuing E2E experiential tasks.

